#### Participants

Since screening will be integrated into the clinical services of the centers, it will be routine clinical care. Coded EHR data with minimal protected health information (PHI) will be collected for patients. Reflecting the importance of staff in implementation [45], consented participants include the site PI and screeners and, in strategy II, the champion.

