#### Procedure

All sites, regardless of randomization to strategy I or II, will participate in a 3-h professionally prepared webinar (develop educational materials, distribute educational materials) at the beginning of their cohort year. The webinar will include all information necessary to understand, access, and deliver the web-based PAT. The webinar will be based on our in-person training program and curriculum [35] modified to integrate feedback from aim 1 interviews. Each site PI, all screeners, and the research coordinator will participate. For sites randomized to strategy II, the champion will attend. We will work with sites to identify this team and the champion (in TIER) “individuals who dedicate themselves to supporting, marketing, and driving through an implementation, overcoming indifference or resistance that the intervention may encounter in an organization” [37].

After the PAT is completed online, it is scored immediately, and a summary of the score and clinical concerns identified is generated. Only coded data will be transmitted to the study data core. A master list for this data will be maintained at each respective study site and will not be shared with the core research team. We will provide support to sites in the technical aspects of the implementation related to using the web-based forms (centralize technical assistance). If we identify any pattern of problems with technical aspects of implementation, we will communicate with sites promptly.

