#### Measurement/outcomes (all sites)

The measures assess outcomes across patient/family, provider, and institution levels (Table 1) that are clearly operationalized and reproducible [46]. Site PIs and coordinators will attend training on data collection procedures, in separate sessions for the two conditions.

**Table 1 Tab1:** Measurement

Level/Hyp	Concept	Source	Metric/measure
Patient/family 2.1	Penetration Health equity	EHR (monthly)	Demographics: race, ethnicity, zip code, insurance No. eligible families, English/Spanish No. eligible families screened, English/Spanish % Family feedback letter provided
Provider 2.2	Feasibility Appropriateness Acceptability Engagement in addressing health disparities Job satisfaction Burnout	Survey (Pre, 6-month, Post)	Acceptability of intervention measure Intervention appropriateness measure Feasibility of intervention measure AREA scale of physician engagement Satisfaction employees healthcare Maslach Burnout Inventory version for Medical Personnel
Institution 2.3	Adoption Sustainability: perceived benefit Cost-effectiveness: services/need and cost	Survey	Site participation rate PAT implementation questionnaire
		EHR (monthly)	Psychosocial Services and Medical Treatment Checklist Intensity of Treatment Rating Scale

At the patient/family level (Hyp 2.1) the site coordinator will extract EHR data and send the coded data via REDCap to the data core. The following data for English and Spanish versions of the PAT will be reported monthly: new patients meeting eligibility requirements per the PAT implementation plan; patients with documentation of PAT screening; patients receiving feedback letter; demographic data on all eligible and all screened (race, ethnicity, zip code, insurance).

At the provider level (Hyp 2.2), the site PI and screeners will complete the following self-report measures (~ 15 min) at baseline (T1), and 6 (T2) and 12 (T3) months via REDCap: acceptability of intervention measure; intervention appropriateness measure and feasibility of intervention measure [47]; measure of physician engagement in addressing racial and ethnic health care disparities [48], satisfaction of employees in healthcare survey [49], and Maslach Burnout Inventory [50].

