The outcomes at the institution level (Hyp 2.3) are as follows: adoption, the intention of sites to use the PAT (the ratio of sites that initiate the study); whether screening is perceived as an asset to the institution using the PAT Implementation Questionnaire (PIQ) [35] which will be completed by the site PI, the screeners, and the champion at T1, T2, and T3; whether services are matched to the needs of families based on PPPHM levels using EHR data using the Psychosocial Services and Medical Treatment Checklist (PSMTC) [18] at 30, 60, and 90 days; cost using the data from the PSMTC to estimate the amount of psychosocial staff time and national median hourly salary data [51–53]. The Intensity of Treatment Rating Scale (ITR-3) [54] will be completed at the 90-day post-screening data collection time point based on diagnosis, stage, and treatment.

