H2.1. ANOVA will compare the effectiveness of the two implementation strategies on penetration and health equity. The outcomes are proportions: families screened/families eligible, families provided feedback/families screened, ethnic minority families screened/ethnic minority families eligible, low SES families screened/low SES families eligible. ICCs among the clusters will be calculated and used to adjust for the cluster effect [67, 68].H2.2. Three sets of outcome variables—perception of implementation, engagement in addressing health disparities, and burnout/job satisfaction—will be tested. A two group analysis using Structural Equation Modeling (SEM) will compare the effectiveness of the two strategies [69, 70]. To test the effect of time, we will conduct latent growth curve analysis [71–73]. Analyses will be conducted using Mplus 5.0 [74] with ML estimation for outcome variables that meet the distribution assumptions, and WLSMV estimation for variables that do not. Potential mediating effects of favorable perception of implementation on provider job satisfaction and burnout will be examined using mediation models. TIER is expected to be associated with more favorable perceptions of implementation, less burnout, and higher job satisfaction.H2.3. At the institution level, adoption of the PAT will be measured by a ratio of sites that initiate implementation/sites that agreed (H2.3a). If substitutions are necessary, sites that are newly invited will be added to the denominator and adoption calculated by total acceptances/total invited. ANOVA will be conducted to compare the effectiveness of the two strategies. For H2.3b sustainability (PIQ perceptions of implementation benefits and challenges), ANOVA will be conducted to compare the effectiveness of the two strategies on benefits and challenges. For H2.3c, we are interested in the extent to which psychosocial care is matched to need. A cost-effectiveness threshold or criterion to which to compare costs of screening with these two implementation strategies has not been established, necessitating our consideration of valued outcomes in the psychosocial screening literature and resources available. We will use a data analytic approach that we used previously [18]. ANOVA will be conducted to test whether psychosocial care is matched with levels of psychosocial risks, resulting in a 2 (strategy) × 3 (psychosocial risks: clinical, targeted, universal) design on equitable distribution of services and costs of care. It is expected that the 3 PPPHM levels will be related to number and costs of services provided as measured on the PSMTC, with least at universal and most at clinical. It is expected that TIER will result in a better match between level of risk and services provided. Scores from the PSMTC will be derived and mapped onto the levels of the PPPHM. Additional analyses will be conducted to compare English speaking and Spanish speaking families, different ethnicity, race, and SES and insurance status on the outcome variables for H2.3c.

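### The champion, a role that exists only in TIER, completes the PIQ at T1, so that baseline cannot wholly precede disclosure of the strategy, and nothing places the other T1 surveys before it

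*Protocol article*

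**What the plan says.** All references are to the protocol article.

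- **Who answers the PIQ.** Under Measurement/outcomes (all sites), the PIQ is "completed by the site PI, the screeners, and the champion at T1, T2, and T3".
- **Who has a champion.** Under Participants (aim 2), "consented participants include the site PI and screeners and, in strategy II, the champion". Under Procedure, "For sites randomized to strategy II, the champion will attend"; this refers to the webinar held "at the beginning of their cohort year". The Strategy II section describes the champion as someone likely to be keen on and committed to universal screening. The Fidelity section has the champion complete an activity questionnaire at the start of the study year.
- **Who answers the H2.2 surveys.** Under Measurement/outcomes, "the site PI and screeners will complete the following self-report measures (~ 15 min) at baseline (T1"), and again at 6 and 12 months (T2, T3). Champions are not named. Table 1 labels the first survey as Pre, without saying before what.
- **Training in data collection.** "Site PIs and coordinators will attend training on data collection procedures, in separate sessions for the two conditions". No date relative to T1 is given.
- **Analysis.** H2.2 is compared by two-group structural equation modelling, and "To test the effect of time, we will conduct latent growth curve analysis". The PIQ (H2.3b) is compared between strategies by ANOVA; how the T1 value enters is not stated.
- **Randomisation.** Sites are allocated first to cohort, then to strategy. When a site learns its strategy relative to T1 is not stated.

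**The concern.** A baseline is useful in a comparison of change because allocation cannot have influenced it. Two things put that in doubt here.

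First, the T1 PIQ depends on allocation through who answers. TIER contributes champions and Training does not, and champions are chosen partly for their favourable view of screening. This difference in respondent mix recurs at T2 and T3, so it can enter any PIQ comparison that pools all respondents.

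Second, the H2.2 and PIQ measures are unblinded self-report. If PIs and screeners answer T1 after learning whether their site gets extra support, ratings of acceptability, appropriateness, feasibility and perceived benefit may already reflect that news. With three time points, T1 anchors the slope, so a shift at T1 passes into the estimated difference in change.

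**Working it through.** **1. Order of events for the champion.** The role exists only at strategy II sites. To have a champion at T1, a site must have been told it is in strategy II and have named someone. The champion's T1 PIQ therefore follows disclosure. This follows from the text without assumption.

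**2. Order of events for PIs and screeners.** The H2.2 surveys share the T1 label but exclude champions, so the argument in step 1 does not carry over. The separate training sessions would disclose the arm to site PIs, but they are undated and do not include screeners. The order is open: the text neither places these surveys before disclosure nor after it.

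**3. Respondent mix in the PIQ.** The Sample size paragraph (Data analysis, Aim 2) gives a staff sample of 45 to 99. With k PIs and screeners per site, the total is 18k + 9:

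- k = 2: 18 × 2 + 9 = 45, as stated.
- k = 5: 18 × 5 + 9 = 99, as stated.

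With 9 sites per arm and the same k in both, TIER has 9k + 9 PIQ respondents and Training has 9k:

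| k | TIER | Training | Champion share of TIER |
|---|---|---|---|
| 2 | 27 | 18 | 9/27 = 33% |
| 5 | 54 | 45 | 9/54 = 17% |

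The shift in the TIER mean from mix alone is the champion share times the champion-versus-other difference. The document gives no value for that difference, so it is assumed:

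| Assumed champion difference | Shift, k = 2 | Shift, k = 5 |
|---|---|---|
| 0.2 SD | 0.07 SD | 0.03 SD |
| 0.5 SD | 0.17 SD | 0.08 SD |
| 0.8 SD | 0.27 SD | 0.13 SD |

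On common roles only, the comparison is 18 v 18 to 45 v 45.

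**4. Effect of a disclosure shift at T1 among PIs and screeners (illustration only).** Assume a true T3 difference of 0.5 SD and a T1 shift s caused by disclosure that has gone by T3. The difference in change is 0.5 − s. With T1 as a covariate and an assumed correlation of 0.5, the adjusted difference is 0.5 − 0.5s.

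| s (assumed) | Difference in change | T1-adjusted difference |
|---|---|---|
| 0.1 SD | 0.4 SD | 0.45 SD |
| 0.2 SD | 0.3 SD | 0.40 SD |
| 0.3 SD | 0.2 SD | 0.35 SD |

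If instead the shift persists unchanged to T3, the observed T3 difference is 0.5 + s and the difference in change is (0.5 + s) − s = 0.5 SD. So even the direction of the net effect depends on whether the shift fades. A T3-only comparison of PIs and screeners does not use T1.

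**The case against.** A reader might infer that all T1 surveys are taken after sites know their strategy, and that the H2.2 growth curves therefore start from contaminated values. The document does not support this. Champions are not H2.2 respondents, T1 may be a window rather than a day, and the training sessions are undated and omit screeners. The exact order of survey and disclosure is the kind of operational detail a journal article can leave to the full protocol. Knowing the arm also makes a shift possible without showing that one occurs, and a shift in burnout or job satisfaction from such news is much less plausible than one in perception ratings. All of this stands.

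A reader might also take the reductions of 20%, 40% and 60% in step 4 (from 0.5 to 0.4, 0.3 and 0.2 SD) as an estimate of bias. They are not one: they rest on assumed shifts that vanish by T3. The plan states no T1 adjustment, and the growth curve is described as testing the effect of time, alongside a separate two-group comparison.

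Finally, the fix has a real difficulty. H2.2(a) concerns how feasible, appropriate and acceptable the strategy is, and staff asked before the webinar may be rating something not yet explained to them. That stands too and limits the fix.

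None of this answers the point about the champion. There the article states the schedule, and the stated schedule cannot give a PIQ baseline that is wholly before disclosure.

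**Conclusion.** The point holds for the PIQ as written. At T1 the champion's answer necessarily follows disclosure, and TIER includes a respondent type absent from Training: 17% to 33% of its respondents, taking the article's staffing counts, equal staffing in the two arms and champions counted in addition to PIs and screeners, as the article does. If champions score an assumed 0.5 SD higher, the TIER mean moves by 0.08 to 0.17 SD from mix alone, with respondents weighted equally.

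For PI and screener surveys the conclusion is weaker: T1 is not shown to precede disclosure, so the starting values of the growth curves can be affected by knowledge of the arm. Whether they are, and by how much, cannot be determined from the document. The exposure is mainly in acceptability, appropriateness, feasibility and PIQ.

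The matter deserves correction because a baseline free of allocation cannot be recovered once a cohort has passed T1.

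**What to change.** 1. Have site PIs and screeners complete T1 after cohort assignment but before the site is told its strategy and before the arm-specific data-collection training. Two-step randomisation already separates the two allocations, so this reorders existing steps.
2. If the acceptability, appropriateness and feasibility measures or the PIQ cannot be answered meaningfully before the common webinar, still collect engagement with health disparities (AREA), job satisfaction and burnout before disclosure. Do not treat the later perception ratings as a baseline free of allocation.
3. Do not count the champion's first PIQ as baseline. Compare the PIQ between strategies on the roles common to both arms (site PI and screeners) and report champions separately.
4. Reconcile the provider-level sample of 45 to 99, which counts champions, with the H2.2 survey text, which does not name them. Without champions it is 18 × 2 = 36 to 18 × 5 = 90.

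Cost: screeners must be named somewhat earlier, and the between-strategy PIQ comparison loses the 9 champions. Cohorts already past T1 keep their data, flagged as not known to precede disclosure.

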#### Data cleaning and missing data

All data will be reviewed for valid values/data entry errors, outliers, and extent/pattern of missing data. Descriptive statistics will be reviewed. Consistency and logic checks will be applied for review/cleaning. The multiple group analysis models will provide valid estimates of efficacy if the proportion of missing values is < 10%. Analysis will be conducted at the patient/family, provider, and institution levels. The effect of program size and cohort will be examined and controlled if needed.

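### Treatment intensity (ITR-3) is collected for hypothesis 2.3 but has no role in the stated H2.3c analysis of services and costs; it should be a prespecified covariate in a model that accounts for site

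*Protocol article*

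**What the plan says.** - **Measurement/outcomes (all sites), Table 1.** For the institution-level hypothesis 2.3, the EHR measures listed for services, need and cost are "Psychosocial Services and Medical Treatment Checklist Intensity of Treatment Rating Scale".
- **Same section, institution-level outcomes.** The checklist (PSMTC) records services at 30, 60 and 90 days and supplies the staff time from which cost is estimated. The text then adds: "The Intensity of Treatment Rating Scale (ITR-3) [54] will be completed at the 90-day post-screening data collection time point based on diagnosis, stage, and treatment".
- **Data analysis, Aim 2, H2.3 (printed under Data cleaning and missing data).** H2.3c is an ANOVA "resulting in a 2 (strategy) × 3 (psychosocial risks: clinical, targeted, universal) design on equitable distribution of services and costs of care". Services and costs are expected to rise from the universal to the clinical level, and TIER is expected to give the better match. The text also points to an approach used in an earlier study (reference 18). Further comparisons are named: "Additional analyses will be conducted to compare English speaking and Spanish speaking families, different ethnicity, race, and SES and insurance status".
- **Data cleaning and missing data, on control variables.** "The effect of program size and cohort will be examined and controlled if needed".
- **Data analysis, Aim 2, H2.1.** "ICCs among the clusters will be calculated and used to adjust for the cluster effect". No such sentence appears under H2.3.

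ITR-3 is not mentioned anywhere in the analysis text.

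**The concern.** The number of psychosocial contacts in the first 90 days plausibly depends on how intensive the child's medical treatment is, as well as on family risk and on how the site was trained. ITR-3 is the one medical case-mix measure planned for this hypothesis, and it sits beside the service checklist in Table 1. The article names a model, a list of further comparisons and a list of control variables for these outcomes, and ITR-3 is in none of them.

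Three things are at stake:

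- **Chance imbalance.** Sites are stratified by size, not by case mix, and there are 9 per arm.
- **Precision.** A prognostic covariate that is already planned would go unused.
- **The match between care and need.** Risk level is observed, not randomised. If intensity is associated with PAT risk, part of the service gradient across risk levels is medical.

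Without a prespecified role for ITR-3, the choice between adjusted and unadjusted results could also be made after the data are seen.

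**Working it through.** **Inputs from the article (Sample size paragraph).** Median new patients per year are 60, 92 and 339, with 6 sites of each size, 9 sites per arm and an ICC of .005. The article gives no ICC for services or cost and no figure for ITR-3, so every other input below is an assumption, shown as a range.

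**1. Site sizes.** 6 × (60 + 92 + 339) = 2946, and half is 1473; both match the article. Mean families per site = 1473/9 = 163.7. Design effect = 1 + (163.7 − 1) × .005 = 1.813. (This gives 1473/1.813 = 812 effective families per arm, not the stated 950. That is a separate matter; step 4 shows the result with either figure.)

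**2. Is the strategy effect biased?** A simulation used 18 sites (three of each size per arm), no true strategy effect and 4000 runs per setting. The assumed between-site ICC of ITR-3 was .005 to .10, and its correlation with services .1 to .5.

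| Result without a true effect | Without ITR-3 | With ITR-3 |
|---|---|---|
| Mean estimated strategy effect | within ±0.003 SD | – |
| Two-sided 5% test at site level | 4.0–5.6% | 4.3–5.4% |
| Family-level test ignoring sites, ITR-3 the only source of clustering | 5–48% | – |
| Same, plus residual ICC of .005 | 18–50% | – |

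Omitting ITR-3 causes no systematic bias, and error is nominal once sites are respected. The inflation comes from ignoring sites.

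**3. How large can chance imbalance be?** With three sites of each size per arm, the large sites supply 3 × 339 = 1017 of 1473 families (69%). The sum of squared site weights is 3 × (60² + 92² + 339²)/1473² = 0.1756, or 1/0.1756 = 5.7 effective sites per arm. With between-site ICC ρ for ITR-3, the SD of the arm difference in ITR-3 is √(2 × [0.1756ρ + (1 − ρ)/1473]).

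- ρ = .005 gives 0.056 SD. At correlation .1 the outcome shift has SD 0.006.
- ρ = .10 gives 0.191 SD. At correlation .5 the outcome shift has SD 0.095, a 95% range of about ±0.19 SD.

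If 40% of patients are high-intensity (assumption), a gap of 10 points is 0.10/√(0.4 × 0.6) = 0.204 SD. The chance of a gap at least that large, in either direction, is about 0.3% at ρ = .01, 14% at .05 and 28% at .10.

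If high-intensity patients receive twice the service hours (assumption), a 45% v 35% split gives (0.55 + 0.45 × 2)/(0.65 + 0.35 × 2) = 1.45/1.35 = 1.07. That is a 7% difference with no strategy effect in that one draw.

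**4. What precision is lost?** With a correlation r between ITR-3 and services within site, adjustment removes r² of the family-level variance: 9% at r = 0.3 and 25% at r = 0.5. Family-level variance is only part of the variance of an arm mean; its share is (1 − ICC)/design effect. Between-site variance is taken as unchanged.

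| ICC and design effect | Family-level share | Reduction in arm-mean variance, r = 0.3 to 0.5 |
|---|---|---|
| .005, 1.813 | .995/1.813 = 0.549 | 5% to 14% |
| .005, design effect implied by 950 (1473/950 = 1.551) | .995/1.551 = 0.642 | 6% to 16% |
| .05 (assumed), 1 + 162.7 × .05 = 9.13 | .95/9.13 = 0.104 | 1% to 3% |

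**5. The risk-level contrast.** The step 3 arithmetic applies to two risk levels in place of two arms. If the shares of high-intensity patients are equal, the distortion is zero. If they are 45% and 35%, it is again 7%, and randomisation of sites does not average it away. The article does not say whether intensity and PAT risk are associated, or in which direction.

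**The case against.** **Silence in a condensed article is not exclusion.** A reader might infer that the trial has decided to leave ITR-3 out. The documents do not support that: covariates are often left to the SAP, and H2.3c refers to an earlier approach whose content is not shown. The further comparisons are group contrasts, not a covariate list. This stands against any claim of deliberate exclusion. It does not remove the point, because the article does state a model and does name control variables, and ITR-3 is in neither. The cited approach neither supplies nor rules out a role for it.

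**Randomisation protects the strategy effect.** A reader might infer that differences in medical treatment between sites will pass for a strategy effect. Step 2 shows otherwise: the error rate of an analysis that respects sites already covers chance imbalance. This objection stands in full for the strategy effect. The 7% figure is one assumed bad draw, not an expected bias.

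**The strategy-by-risk interaction.** Systematic distortion would need the link between intensity and PAT risk to differ by arm. Nothing in the article says it does, and the PAT subscales it lists do not include treatment intensity. So the exposed contrast is that between risk levels, and only if the association exists.

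**Timing and selection.** ITR-3 is recorded after randomisation, and a risk level requires a completed PAT. H2.1 predicts that TIER screens more families, so the analysed families may be selected differently by arm. Adjustment helps with this but does not settle it. Nor does the article say which families are rated on ITR-3; that every assessed family will be rated is an inference.

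**Conclusion.** The point holds as a modest improvement to a stated model. ITR-3 is planned for hypothesis 2.3 and has no stated role in H2.3c. Its omission does not systematically bias the strategy effect. What remains is:

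- chance imbalance in case mix with 9 sites per arm, about 5.7 in effect if sizes follow the medians;
- a precision loss that is small to moderate at the article's ICC and slight at a higher one;
- a non-randomised risk-level contrast open to confounding if intensity is associated with PAT risk.

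The sizes rest on assumed correlations and assumed between-site variation in intensity, and on an ICC that the article states for its family-level sample size, not for services or cost. The larger threat to error rates in H2.3c is a family-level ANOVA without allowance for site. Adding ITR-3 while leaving that in place would not be enough.

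**What to change.** In the H2.3c analysis:

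1. Prespecify ITR-3 level as a covariate in the models for number and cost of services, beside strategy, risk level and their interaction.
2. Extend the allowance for clustering by site to these models, with degrees of freedom suited to 18 sites.
3. Report the result without ITR-3 alongside.
4. State the assumption that the implementation strategy does not alter diagnosis, stage or treatment, since ITR-3 is recorded 90 days after screening.
5. State which families are rated, and that adjustment does not fully remove selection if the proportion screened differs by arm.

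The cost is wording in the analysis plan, as the data are already to be collected. The small downside is reliance on the assumption in item 4 for a covariate recorded after randomisation; the unadjusted result in item 3 lets readers judge it.
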